### Secondary study parameters

Binary secondary outcome variables (i.e., having received any secondary surgical procedure, experienced any type of complication, showing stability and alignment on weight bearing radiographs) will be compared between groups using Pearson’s Chi-squared test. In case of expected cell counts of less than five we will use Fisher’s Exact test.

Continuous secondary outcomes (i.e., scores on the AOFAS, SF-12, FADI, MCQ, and PCQ) will be analysed using a linear mixed-effects regression model, similar to the analysis of the primary study parameter.

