## Diagnosis and treatment

An inadequately treated Lisfranc injury with persistent instability can result in multiple late complications, most commonly painful instability of the joint malformation or post-traumatic arthritis [16, 17]. All these complications can lead to gait dysfunction and foot pain [16, 17]. Therefore, adequate surgical treatment is needed to restore stability. Due to the diversity of injuries, there is no gold standard for treating all Lisfranc injuries in a similar manner [10]. It is therefore important to distinguish between ligamentous Lisfranc injuries and Lisfranc fracture dislocation.

PA is generally accepted as the treatment of choice in pure ligamentous injuries. In case of an unstable Lisfranc injury, with displacement either on static or dynamic radiographic evaluation, the best treatment is aimed at a stable construction with anatomic alignment [10]. This can be achieved by using either ORIF or by PA. ORIF is associated with problems such as the occurrence of secondary arthritis in 40–90% and the need for secondary interventions to perform arthrodesis or to remove the osteosynthesis materials in order to relieve pain [18, 19]. To prevent this need for secondary interventions and the development of post-traumatic arthritis, primary arthrodesis is suggested [6, 7, 12, 20]. On the other hand, retaining the joints of the midfoot may possibly improve the functional mobility and thereby the quality of life after removal of the osteosynthesis materials. As these potential complications can have a major impact on patients’ everyday lives, research is needed to define the best available surgical treatment for these patients with unstable Lisfranc fracture injury.

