## Methods

### Aim of the study

The primary objective of this study is to compare the effects ORIF vs. PA have on the quality of life of patients with unstable or displaced Lisfranc fractures over a period of 24 months.

The secondary objectives are to compare the differences in the amount and type of secondary procedures, including removal of osteosynthesis materials, difference in objective and subjective functional outcomes, difference in alignment of the foot on weight-bearing X-rays, difference in occurrence of complications and differences in costs and cost-effectiveness.

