### Primary arthrodesis

PA, stabilization by fusion, is the other surgical intervention of choice in the treatment of Lisfranc injury. After surgical exposure, cartilage of the involved unstable joints ray 1–3 of the Lisfranc injury will be removed and after reduction, fixation will be done by osteosynthesis with bone graft if necessary. Osteosynthesis will be done by using bridge plate (variable angle locking plate and/or locking plate and/or dynamic compression plate—3.5 mm, 2.7 mm or 2.4 mm) and/or trans articular screw osteosynthesis (4.0 mm cannulated screws and/or solid small fragment screws and/or HCS).

The tarsometatarsal joints 4–5 are essential joints to remain dynamic and the consensus is to fix these using some temporary fixation device, mostly K-wires if remaining dislocated after arthrodesis of the first 3 TMT joints.

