### Secondary outcomes

Secondary outcomes are the differences in the amount and type of secondary procedures (including removal of osteosynthesis materials). The most important complications are post-traumatic arthritis, infection, persistent instability, non-union and foot deformity (pes planovalgus). The frequency of all complications will be measured using post-surgery follow-up visits. The differences in objective and subjective functional outcomes; active range of motion as determined by the online questionnaires: American Orthopaedic Foot and Ankle Society Score (AOFAS), Short Form Health Survey (SF-12), and Foot and Ankle Disability Index (FADI). The range of motion will also be measured at the clinical follow-up visits. The difference in alignment of the foot on weight-bearing X-rays (stability) which will be measured at the clinical follow-up moments. Secondary economic outcomes are the patient, family and societal health care costs, and the cost-effectiveness as measured with the online Medical Consumption Questionnaire (MCQ) and Productivity Costs Questionnaire (PCQ).

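### The secondary outcome is the amount and type of procedures and complications, but the analysis names only any/none composites that can blur or mix technique-linked events

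*Protocol article*

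**What the plan says.** The objective, in the protocol article under Aim of the study, is to "compare the differences in the amount and type of secondary procedures, including removal of osteosynthesis materials". The Secondary outcomes section repeats it as "differences in the amount and type of secondary procedures (including removal of osteosynthesis materials" and then names the complications of interest: "The most important complications are post-traumatic arthritis, infection, persistent instability, non-union and foot deformity (pes planovalgus".

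Under Secondary study parameters, the binary outcomes are introduced by "i.e." and spelled out as "having received any secondary surgical procedure, experienced any type of complication, showing stability and alignment on weight bearing radiographs". They "will be compared between groups using Pearson’s Chi-squared test", with Fisher's exact test when expected counts are below five. The article names no count, no breakdown by type, and no separation of planned from unplanned removal.

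Two other parts of the article bear on this:

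- **K-wires.** The ORIF section uses K-wires for TMT 4 and/or 5. The Primary arthrodesis section says of these joints that "the consensus is to fix these using some temporary fixation device, mostly K-wires", on condition that they are still dislocated after the first three are fused. Only the latter section calls the fixation temporary.
- **Arthritis.** Under Diagnosis and treatment, "ORIF is associated with problems such as the occurrence of secondary arthritis in 40–90" per cent, and PA is described as a way to prevent arthritis and secondary interventions. PA removes cartilage only from the involved unstable joints of rays 1–3.

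**The concern.** A patient with one screw removal and a patient with three unplanned reoperations score the same on an any/none variable. A patient with a superficial infection scores the same as one with disabling arthritis. The analysis as named therefore cannot deliver the amount and type that the objective promises.

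Two features make the loss of detail matter more here than in most trials:

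- **Planned removal.** Removal of osteosynthesis materials is explicitly a secondary procedure, and nothing excludes scheduled removal of temporary fixation. If it counts, the procedure composite contains events that say nothing about failure of either technique.
- **Technique-linked complications.** Arthritis is prevented by PA in the joints that are fused. Non-union, in the sense of failed fusion, arises only after PA. Pooled with infection, instability and deformity, these two components can dominate the result or offset each other.

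Reoperations and complications are central to the article's case for changing practice, so a result that does not show what differs would be of limited use.

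**Working it through.** **The plan's own figure.** The sample size rests on EQ-5D-5L: SD 0.15, difference 0.08, 80% power, two-sided 5% (sidedness assumed). n = 2 × (1.960 + 0.842)² × 0.15² / 0.08² = 55.2, so 56 per arm, as stated (80.6% power at 56). The plan gives no power for the binary secondary endpoints. Below, 56 per arm is taken from the plan. Every event rate is an assumption except the 40–90% arthritis after ORIF.

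**Formulas.** With independent events of probability k and p, the chance of at least one is k + (1 − k)p. For two proportions a and b with mean m and n = 56 per arm:

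- se0 = √[2m(1 − m)/n]
- se1 = √{[a(1 − a) + b(1 − b)]/n}
- power = Φ[(|a − b| − 1.96 × se0)/se1]

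**Planned removal equally common in both arms.** Assume unplanned surgery in 50% (ORIF) vs 20% (PA).

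| Planned removal counted, each arm | Any procedure, ORIF vs PA | (Difference − 1.96 × se0)/se1 | Power |
|---|---|---|---|
| 0% | 50% vs 20% | (0.30 − 1.96 × 0.0901)/0.0856 = 1.44 | 93% |
| 30% | 65% vs 44% | (0.21 − 1.96 × 0.0941)/0.0920 = 0.28 | 61% |
| 50% | 75% vs 60% | (0.15 − 1.96 × 0.0885)/0.0874 = −0.27 | 39% |

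For the second row, 0.30 + 0.70 × 0.50 = 0.65 and 0.30 + 0.70 × 0.20 = 0.44. The true difference in unplanned surgery is the same in all three rows.

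**Planned removal unequal, unplanned surgery 15% in both arms.** With planned removal in 50% vs 20%, the composite is 0.50 + 0.50 × 0.15 = 57.5% vs 0.20 + 0.80 × 0.15 = 32%. This is significant 78% of the time, although unplanned surgery does not differ. With equal planned removal (30% in both), the composite is 40.5% in both arms and no such difference arises.

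**Any complication.** Assume a 10% risk of the other shared complications in both arms.

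| Arthritis, ORIF | Arthritis, PA | PA non-union | Any complication, ORIF vs PA | Power |
|---|---|---|---|---|
| 40% | 0% | none | 46% vs 10% | 99% |
| 40% | 10% | none | 46% vs 19% | 87% |
| 40% | 20% | none | 46% vs 28% | 51% |
| 65% | 20% | none | 68.5% vs 28% | over 99% |
| 40% | 0% | 40% | 46% vs 46% | no difference to detect |

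First row: 0.40 + 0.60 × 0.10 = 0.46. Last row, PA: 0.40 + 0.60 × 0.10 = 0.46. The 40% non-union is a deliberately extreme value, chosen to show complete cancellation. Partial cancellation needs less.

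In the first four rows the result comes from arthritis alone. In the last row, two large and opposite differences vanish.

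**The case against.** The other side has a good deal of right on it.

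- **Planned K-wire removal is not stated to count.** A reader might infer that every patient with K-wires becomes an event. The article does not say so: only the PA section calls this fixation temporary, its use there is conditional, and neither section says how its removal is classified. What stands is that the wording allows it to count.
- **Dilution is not bias.** Removal that is equally common in both arms lowers power but creates no false difference. Only unequal use or removal does that.
- **Implant removal belongs in the outcome.** It is deliberately included and is a legitimate measure of patient burden.
- **The complication test is not settled in advance by technique.** That inference is tempting from the 99% figure, but the figure sets arthritis after PA to zero. TMT 4–5 and other unfused joints remain at risk, so a PA patient can still develop arthritis, and non-union can offset the advantage of PA.
- **Less arthritis is a real effect of PA.** Preventing it is the stated reason for the operation. The composites are therefore not uninterpretable and do not answer a wrong question. For the same reason, limiting the pooled endpoint to complications possible in both arms would remove PA's main expected benefit and its specific harm. That is a debatable trade-off and is not recommended here.
- **Detail may sit elsewhere.** Late complications and re-interventions are recorded at each follow-up, and event definitions or tables by type may be in a full protocol or analysis plan that is not shown.

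The last point does not remove the mismatch. The article does not leave the variables open: it names them and their test, and they differ from the outcome it states.

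**Conclusion.** The concern holds as a mismatch between the stated secondary outcome and the stated analysis. Amount and type are promised; any/none is analysed. The composites are valid randomised comparisons, but coarser than the question asked, and neither a significant nor a null result would show which procedure or complication differs.

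Under the assumed rates, counting planned removal equally in both arms costs 32 to 54 percentage points of power (93% to 61% or 39%). For complications, arthritis at the lower end of the article's 40–90% range gives anything from a near-certain significant result to no difference at all, depending on arthritis in unfused joints and on non-union after PA. These figures rest on independence of events and on assumed rates, so they show that the problem can be large, not how large it will be. Only secondary endpoints are involved.

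**What to change.** Keep both composites and add the following:

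1. State whether planned removal of temporary fixation counts in the any-procedure composite, and do not count it as an unplanned reoperation.
2. Analyse implant removal and unplanned reoperation as separate endpoints.
3. Compare the number of procedures per patient with a Poisson or negative binomial model, with follow-up time as offset.
4. Compare complications by type, with arthritis and non-union shown separately beside the composite.

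The cost is a few more secondary tables and, if the case report form lacks one, a field for the reason for each procedure. The added comparisons bring more secondary tests, to be read as such. Sample size, follow-up and the primary analysis do not change.

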## Economic evaluation

A trial-based economical evaluation will be completed from a societal and healthcare point of view with a total follow-up period of 24 months, and this evaluation is in line with the Dutch guidelines for health economical evaluation [28]. The Dutch costing manual is the source for the valuation of the cost prices [27]. The so called ‘friction cost method’ will be calculating the amount of absence of work of each included participant in this study. This ‘friction cost method’ is recommended by the Dutch manual for costing [29]. The cost-effectiveness in this study will be measured in societal cost per QALY, as based on the EQ-5D-5L questionnaire. Subsequently the sensitivity and the bootstrap analysis will be conducted to notice possible uncertainty. To visualize the chance of the cost-effectiveness of the two interventions cost-effectiveness acceptability curves will be constructed. Subsequently, sensitivity analyses will be performed on the data input for testing the strength of the study results. Besides, in accordance with the Dutch guidelines for economic evaluations as well as the ISPOR guidelines, a budget-impact analysis (BIA) will be performed [30].

## Data

### Data management

The study participants will all receive a special participant identification codification. This codification consists of four capital letters (A, B, etc.) indicating the medical institution of inclusion and is followed by three numbers (001, 002, etc.) indicating the order of inclusion in the study. The BFF study team, the Health Care Inspectorate, and the monitor from the external clinical trial organization; Clinical Trial Management Maastricht (CTCM) will have access to this private participant data. Data will be archived in a password protected digital database. The CI will secure the key to the participant identification codification and the private participant related data. The data will be saved for 15 years after finalization of the study. A full Data Management Plan can be obtained by contacting the CI of the BFF Study.

### Data protection

All data concerning participants or their participation in this trial will be considered confidential and handled in compliance with all appropriate regulations. Only the LI, side investigators, CI and monitor of the study have access to these patient data.

### Data safety monitoring

The CTCM is independent from the sponsor of the study and will be monitoring this study. The duties of the CTCM include checking the IC of each included participant, reported AE’s and SAE’s, participant characteristics, and check the completeness of the electronic CRF and if this CRF is corresponding with the EPF. The monitoring includes one site initiation visit (SIV), one monitoring visit after five participant inclusions in the medical institution and one close out visit per participating medical institution of the study.

## Benefits and risks assessment, group relatedness

Literature indicates that both treatment options in this study, ORIF or PA, are accepted for Lisfranc injury. No clear advantage for one treatment option is found at present in the literature. Both treatment options have their known complications, related to the injury itself and the surgical procedure: stiffness of the joint and pain due to arthritis, persistent instability, nonunion, infection, anesthesiologic complications, and hardware failure. But this risk of specific complications is low and generally similar in both treatment options.

During the normal follow-up visits, patients will have to fill in health questionnaires before the appointment at the hospital and will be seen by the treating physician, the researcher, or an independent research assistant. This will take an extra 5–15 min of the patient’s time per visit to the outpatient clinic. Other aspects of the follow-up are identical to that of standard treatment.

In the Netherlands, the annual incidence of Lisfranc fractures is estimated 0.2% of the total number of 300,000 fractures in the Netherlands [16, 28, 29]. Lisfranc injuries are thereby uncommon, but the impact of this injury to the well-being of the patient is significant [24] and up to 20–30% of injuries can be missed during the initial assessment [30].

If this study shows that performing an PA reduces complications, improves outcome, and reduces costs, standard practice can be changed so as to spare patients the disadvantages, such as reinterventions, longer hospital stays, and/or reduction of societal impact. Direct and indirect healthcare costs will be reduced, resulting in savings of €10.4 million euro per year as calculated [4, 6, 18, 19], as well as further savings if the findings are applied to other fractures of the foot, such as Chopart, intertarsal and subtalar injuries. The findings will also be used to design the first national guidelines for the treatment of foot injuries, leading to enhanced quality and continuity of healthcare.

This study will not only provide data concerning the optimal treatment of fracture dislocations of the midfoot, but this study will also provide a framework for individualized patient centered surgery balancing the advantages and disadvantages of retaining or removing a joint in the foot after trauma. Finally, this study will increase the evidence-based level of guidelines in trauma surgery.

## Compensation for injury

There is no need for a liability insurance for the subjects participating in this study since there is no higher risk when included in the study in comparison with the standard care for this injury. There is only need for a regular liability insurance of the hospitals participating in this study.

## Auditing of the participating medical institutions

Auditing will be performed by the CTCM and will be independent from investigators and the sponsor.

## Protocol amendment

In the case of any modifications of the study protocol that may impact the conduct of the study will be communicated to the Medical Research and Ethics Committee Zuyderland.

## Publication policy

Publication will be in accordance with international recognized scientific and ethical standards concerning publications and authorship, including the Uniform Requirements for Manuscripts Submitted to Biomedical Journals, established by the International Committee of Medical Journal Editors.

## Discussion

This protocol publication presents a prospective, randomized, multicenter trial including 13 participating hospitals in the Netherlands. It gives detailed information of study aim, the study method such as the patient flow, patient randomization procedure and recruitment, treatment aftercare and methods of analysis of the collected data and ways to present and publish the results.

This study contains several limitations. Patient blinding was not possible, depending on the surgical treatment and follow-up. Another limitation is within the outcome measure (AOFAS) which has limited validity for this type of injury. Although this might constitute a limitation, the AOFAS Midfoot Scale is the most commonly used outcome measure for patients treated for Lisfranc injury, providing a tool for comparing other studies. Besides this, the FADI questionnaire is used as additional secondary outcome measurement.

The strength of this study is that this is the first study with enough power (n = 112) to define the optimal treatment for patients specifically with Lisfranc fracture dislocation, either PA or ORIF. The study applies to quality of life, type and number of complications, secondary surgical interventions, functional outcomes, and cost effectiveness with an adequate number of patients.

The current literature generally provides poor methodological quality studies with a limited number of patients, which makes it difficult to favour one intervention over the other. Furthermore, the current literature does not investigate specific Lisfranc fracture injuries. To our knowledge there are no previous reported studies or running studies at present which explicitly investigate the unstable Lisfranc fracture injury. In the BFF Study not only the displaced injuries at static radiographic evaluation, but also the non-displaced injuries with instability at dynamic radiographic evaluation, weight bearing radiographs or fluoroscopic stress testing under anesthesia, are also included. At last, the cost measurement, including family and societal costs is not included in previous studies. Cost considerations might be decisive in decision making especially when both treatments are equal based on PROMs. This study will have enough power to determine the optimal treatment for the unstable Lisfranc fracture injury, displaced at static a/o dynamic radiographic evaluation, with the best cost-effectiveness.

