**Discussion:**

This study protocol provides a comprehensive overview of the aims and methods of the attached clinical study. Limitations of this study are the absence of patient blinding since it is impossible in surgical intervention, and the outcome measure (AOFAS) that has limited validity not for these injuries. This study will be the first with enough power to define optimal treatment for Lisfranc fracture dislocations. This is necessary since current literature is unclear on this topic.

*Trial registration* Current controlled Trial: NCT04519242 with registration date: 08/13/2020. Retrospectively registered; Protocol date and version: Version 4 05/06/2020

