### Sample size and feasibility

The primary outcome is quality of life over the follow up period, quantified using the EQ-5D-5L score. The longitudinal analysis will include multiple observations per patient, but it is unclear how strong consecutive measurements are correlated. For that reason, we performed a sample size calculation for a cross-sectional contrast between the two groups, so that even with near-perfect correlation, we would have sufficient power to detect a clinically meaningful difference.

The estimated standard deviation (SD) of the EQ-5D-5L scores is 0.15. To be able to have sufficient statistical power (i.e., 80%) to detect a clinically meaningful difference in QoL of 0.08 points, we need to include 56 patients per group, or 112 in total. We estimate, based on previous experience, that we would need to screen approximately 190 patients to find 112 patients eligible and willing to participate.

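### The Discussion claims adequate numbers for complications, secondary surgery and cost-effectiveness, but adequacy of n = 112 is shown only for an EQ-5D-5L difference of 0.08

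*Protocol article*

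**What the plan says.** Sample size and feasibility names the outcome being sized: "The primary outcome is quality of life over the follow up period, quantified using the EQ-5D-5L score". It gives the spread, "The estimated standard deviation (SD) of the EQ-5D-5L scores is 0.15", and the target, "To be able to have sufficient statistical power (i.e., 80%) to detect a clinically meaningful difference in QoL of 0.08 points". The result is 56 per group, 112 in total. No other outcome has a sample size, an assumed rate, a target difference or a stated power.

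The Discussion goes further. It says "this is the first study with enough power (n = 112) to define the optimal treatment". The next sentence lists quality of life, type and number of complications, secondary surgical interventions, "functional outcomes, and cost effectiveness with an adequate number of patients". The section ends with "This study will have enough power to determine the optimal treatment for the unstable Lisfranc fracture injury", and that sentence goes on to mention the best cost-effectiveness. The abstract makes a general claim of the same kind: "This study will be the first with enough power to define optimal treatment for Lisfranc fracture dislocations".

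Benefits and risks assessment says that "this risk of specific complications is low and generally similar in both treatment options". Secondary study parameters compares binary outcomes (any secondary procedure, any complication, alignment) with Pearson's chi-squared test, or Fisher's exact test when expected counts fall below five.

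**The concern.** The article attaches a power property to outcomes for which it was never calculated. The number needed to detect about half a standard deviation on a continuous score says nothing direct about a comparison of two proportions. When events are rare and rates are close, 56 per arm is few.

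The consequence lies in interpretation. The article expects its findings to feed national guidelines. It ties a change of practice to whether arthrodesis reduces complications, improves outcome and reduces costs. With adequacy already claimed in print, a non-significant chi-squared test on complications or re-operation is easily read as good evidence of no difference.

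**Working it through.** **1. The plan's own figure.** Inputs from Sample size and feasibility: difference 0.08, SD 0.15, power 80%. Descriptive statistics gives a significance level of 0.05. Sidedness is not stated, so two-sided is taken.

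n per arm = 2 × (1.960 + 0.842)² × (0.15/0.08)² = 2 × 7.849 × 3.516 = 55.2, rounded up to 56, or 112 in total.

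Power at 56 per arm is 0.806 (normal approximation). A one-sided test would need 44 per arm, so two-sided is the reading that reproduces the plan. There is no arithmetic error here.

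**2. Binary outcomes at 56 per arm.** Power is the sum of the binomial probabilities of all pairs of event counts for which the uncorrected Pearson statistic reaches 3.84. Losses to follow-up are ignored. The article gives no event rates for the tested endpoints, so all rates below are assumptions shown as a range.

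| Rates compared | Power, Pearson |
|---|---|
| 5% vs 10% | 0.16 |
| 10% vs 20% | 0.32 |
| 20% vs 30% | 0.23 |
| 15% vs 40% | 0.86 |
| 20% vs 50% | 0.93 |
| 10% vs 40% | 0.97 |

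For 5% vs 10% the expected count is 56 × 0.075 = 4.2. This is below five, so the plan's switch to Fisher's exact test would apply at those rates. Fisher's test alone has power of about 0.08 there.

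**3. Smallest gap with about 80% power at 56 per arm.**

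| Lower rate | Higher rate | Gap (points) | Power |
|---|---|---|---|
| 5% | 22.5% | 17.5 | 0.80 |
| 10% | 31% | 21 | 0.81 |
| 20% | 44.5% | 24.5 | 0.81 |
| 40% | 66.5% | 26.5 | 0.80 |

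The detectable gap is therefore about 17 to 27 percentage points over these base rates.

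**4. Numbers needed for smaller gaps.** n per arm = 7.849 × [p1(1 − p1) + p2(1 − p2)] / (p1 − p2)².

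- 5% vs 10%: 7.849 × 0.1375 / 0.0025, about 432.
- 10% vs 20%: 7.849 × 0.25 / 0.01, about 196.
- 20% vs 30%: 7.849 × 0.37 / 0.01, about 290.

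**5. Functional scores.** The primary calculation is a standardised difference of 0.08/0.15 = 0.53 SD. It applies equally to any continuous score for which 0.53 SD is the difference of interest.

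**6. Cost-effectiveness.** Economic evaluation plans bootstrapping and acceptability curves. No cost variance, target or power is given, so no power figure can be derived.

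**The case against.** A reader might infer from the power table that the Discussion's claim is simply false for every binary outcome. The document does not support that. It gives no rates or target differences for the tested endpoints, and assumed rates cannot prove a statement false.

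The remark about low risk concerns specific complications, whereas the planned tests are on composites: any complication and any secondary procedure. Post-traumatic arthritis is listed among the main complications, and Diagnosis and treatment puts secondary arthritis after ORIF at 40–90%. The composite may therefore be common in that arm. Secondary procedures include implant removal, and the Background expects fewer of them after arthrodesis. A gap of 25 to 30 points would be detected with good power (0.86 for 15% vs 40%, 0.93 for 20% vs 50%), and nothing in the article excludes it. All of this stands.

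It also stands that the 0.53 SD calculation carries over to continuous functional scores, that the economic analysis is estimation rather than a significance test, and that no passage says a non-significant secondary result will be reported as no difference.

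It could further be said that detectable differences for secondary outcomes are usually left to a full protocol or analysis plan. That is fair as to omission. The point here is a positive statement of adequacy that the article makes and does not support.

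**Conclusion.** The claim is wrong as written, to a limited extent that differs by outcome.

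- **EQ-5D-5L:** adequacy is shown for a difference of 0.08 under the stated SD.
- **Specific complications:** the claim conflicts with the article's own description of low and similar risk. Power is about 16% to 32% even for a doubling from 5% or 10%.
- **Composite complications and secondary surgery:** unsupported, not false. Power reaches 80% only for gaps of about 17 to 27 points, and the article does not say whether gaps of that size are expected.
- **Cost-effectiveness:** cannot be judged from the document.
- **Functional scores:** no inadequacy is shown.

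The figures rest on two-sided 5% testing, 56 analysed per arm, no dropout and assumed event rates. Losses would reduce power: at 50 per arm, 10% vs 31% falls from 0.81 to 0.77. The sample size itself is not in question.

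**What to change.** In the Discussion, and in the general power statement in the abstract, limit the claim to what was calculated: 80% power for an EQ-5D-5L difference of 0.08 with SD 0.15. State that complications, secondary procedures and cost-effectiveness will be estimated with 95% confidence intervals, by bootstrap for cost-effectiveness. Give the detectable difference for binary outcomes, about 17 to 27 percentage points at 56 per arm depending on the base rate. Add that a non-significant result on these outcomes will not be interpreted as no difference.

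The cost is wording only. No extra patients are needed, and no endpoint or test changes. The one drawback is that the stated reach of the trial becomes less favourable.
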